### Recruitment {15}

To account for a 10% dropout rate, the sample size increased to 1096 participants (548 in the azvudine group and 548 in the control group). To enrol enough participants, we set up special screening staffs in the fever clinic and emergency department where COVID-19 patients often visit, and screening staffs distribute COVID-19 antigen to suspected fever patients to identify candidates. In order to complete such large amount patients’ selection as soon as possible, we selected 46 study sites localized in 17 different provinces in China Mainland; thus, we will obtain timely enrolment to the greatest extent possible.

## Assignment of interventions: allocation

### Sequence generation {16a}

Eligible patients will be randomized in a 1:1 ratio to receive azvudine tablets or placebo only and receive the standard treatment strategy immediately after signing the informed consent form. The permutated-block randomization sequence is generated by computer, and randomization will be performed on a web-based randomization system.

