### Exclusion criteria

Known or suspected allergy to the components of azvudine tabletsPatients diagnosed with severe or critical COVID-19 infection on screeningPatients with severe liver disease (total bilirubin ≥ 2 × upper limit of normal [ULN], alanine aminotransferase [ALT], and aspartate aminotransferase [AST] ≥ 3 × ULN)Patients with severe renal insufficiency (glomerular filtration rate ≤ 60 mL/min/1.73 m^2^) or currently on continuous renal replacement therapy, haemodialysis, and/or peritoneal dialysisPatients with malabsorption syndrome or any other condition compromising gastrointestinal absorption or patients requiring parenteral nutrition or with difficulty taking the investigational product orallyPatients with known HIV infectionPatients with diabetic ketosis or a hyperosmolar hyperglycaemic statePatients with a total neutrophil count < 750 cells/LPregnant or lactating women or those who plan to have a child during participation in this study and within 6 months after the end of this studyPatients currently participating in another interventional clinical trial or who are currently using another investigational productPatients with other uncontrolled active infections (must be aetiologically confirmed) in addition to COVID-19 infectionThe presence of any comorbidities requiring hospitalization and/or a surgical procedure within 7 days prior to the start of this study or a comorbidity considered life-threatening within 30 days prior to the start of this study, as determined by the investigatorPatients who have received or are expected to receive convalescent plasma for COVID-19Patients previously treated with antiviral agents that have been proven to be effective against COVID-19, including but not limited to nirmatrelvir/ritonavir or molnupiravirPatients with other conditions that make it inappropriate for the participant to take part in this trial at the investigator’s discretion

The risk factors for critical infection described in the inclusion criteria and the adverse drug reactions and patient comorbidities that may affect clinical outcomes described in the exclusion criteria were derived from reported studies [19, 20].

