### Who will take informed consent? {26a}

The informed consent will be obtained from COVID-19 patients who meet all inclusion criteria and does not meet any exclusion criteria.

Before being enrolled in the trial, a researcher who has received training will provide patients and their families with an introduction to the study’s purpose and content. The potential benefits and risks will also be explained to them. A 24-h timeframe will be given to the patients and their families to decide whether to participate in the trial, ensuring that their participation is completely voluntary. Additionally, it will be clarified to the patients that their decision to participate or not will have no impact on their regular treatment. Any identifying information, such as names and hospital numbers, will be encoded to maintain confidentiality. The personal information of all participants will always be kept private.

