### Participant timeline {13}

After randomization, patients will receive the allocated interventions for 7 continuous days and be followed up for 6 months. The study schedule includes a screening visit; four treatment visits on day 1, 3, 7, and 14; and three follow-up visits on day 28, 3, months and 6 months. We will collect the patients’ survival status at follow-up visits. The participant timeline is shown in Table 3.

**Table 3 Tab3:** Schedule of screening, intervention and follow-up of the trial

Study periods	Screening	Treatment periods						Follow-up periods		
Time line		d1	d3 + / − 1	d4 to d6^a^	d7 + / − 1	d8 to d13^a^	d14 + / − 2	D28^a^ + / − 3	3 M^a^ + / − 7	6 M^a^ + / − 7
Consent form	X									
Check with inclusion and exclusion criteria	X									
Demographic characteristics	X									
Symptoms	X	X	X	X	X	X	X	X	X	X
Vital sign	X	X	X		X		X			
Adverse event		X	X	X	X	X	X			
Viral load		X	X		X		X			
Chest image (DXR or CT)		X			X		X	X		
Pregnancy test	X						X			
Blood routine	X	X	X		X		X			
Ferritin		X								
Interleukin-6		X								
Hypersensitive C-reactive protein		X	X		X		X			
Blood biochemical test	X	X	X		X		X			
Coagulation		X			X					
Oxygen level	X									
Cardiac troponin and N-terminal pro-brain natriuretic peptide		X			X					
Concomitant medication		X								

^a^Visits by phone calls

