## Statistical methods

### Statistical methods for primary and secondary outcomes {20a}

All data will be analysed using SAS software, version 9.4 (SAS Institute Inc., USA). A two-tailed *p* < 0.05 will be considered statistically significant in all statistical tests (except for the main efficacy indicators and other specified instructions).

The full analysis set (FAS), modified intention-to-treat set (mITT), per-protocol set (PPS), and safety set (SS) will be divided for analysis. FAS includes all eligible and randomized patients. PPS includes eligible patients with better compliance (80–120%), and completing necessary items of CRF.SS includes all patients enrolled in the study who have received at least one dose of medication and have at least one safety evaluation. Baseline characteristics analysis will be based on FAS, efficacy analysis will be based on FAS and PPS, and safety analysis will be based on SS. Unblinded patients will be excluded from PPS.

Continuous data will be summarized as the mean ± standard deviation, median, minimum, maximum, lower quartile, and upper quartile. Categorical data will be presented and summarized as frequencies and percentages in each category.

Between-group comparisons will be conducted by using paired *t*-tests or Wilcoxon rank tests for continuous data, chi-square tests or Fisher exact tests for categorical data, Wilcoxon rank tests or CMH tests for ranked data, and Kaplan‒Meier estimates for time-to-event data. The principles of intention-to-treat analysis will be used.

Efficacy analysis will be based on FAS and PPS. The primary efficacy endpoints are COVID-19-related critical illness and all-cause mortality within 28 days (whichever happens first), which will be analysed based on a time-to-event manner. Kaplan‒Meier method will be used to describe the incidence rates of the primary endpoint in each group separately at 28 days. Between-group comparisons will be performed by the log rank test. A Cox regression model will be used to estimate the hazard ratio and corresponding 95% confidence interval and adjust for potential covariates such as centres. Secondary efficacy endpoint analysis will be performed according to general statistical considerations. The specifics of these methods will be thoroughly outlined in the statistical analysis plan.

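### The full analysis set is restricted to eligible patients despite an intention-to-treat claim; separately, consent, eligibility testing and randomisation are not given one workable order

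*Protocol article*

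**What the plan says.** **Analysis sets.** In Statistical methods for primary and secondary outcomes {20a}, "FAS includes all eligible and randomized patients". The per-protocol set is also confined to eligible patients, with added conditions on compliance and case report form completion. Efficacy is to be analysed on these two sets, and the same section says that intention-to-treat principles apply. A modified intention-to-treat set is named there, and Interim analyses {21b} uses it, but the article does not define its membership.

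**Order of steps.** Who will take informed consent? {26a} states: "The informed consent will be obtained from COVID-19 patients who meet all inclusion criteria and does not meet any exclusion criteria". It adds: "A 24-h timeframe will be given to the patients and their families to decide whether to participate in the trial". Sequence generation {16a} opens with "Eligible patients will be randomized in a 1:1 ratio" and continues that they "receive azvudine tablets or placebo only and receive the standard treatment strategy immediately after signing the informed consent form".

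**Schedule.** Participant timeline {13} says: "The study schedule includes a screening visit; four treatment visits on day 1, 3, 7, and 14". In Table 3 the screening column holds the consent form, the row "Check with inclusion and exclusion criteria", the pregnancy test, the routine blood count and the biochemistry. Day 1 is a separate column. No order is given within screening.

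**Criteria that need a test.** The inclusion criteria require a negative urine pregnancy test in women of child-bearing age. The exclusion criteria set limits for bilirubin, ALT and AST, for neutrophils, and for renal function ("glomerular filtration rate ≤ 60 mL/min/1.73 m^2").

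**The concern.** There are two separate points.

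1. Intention-to-treat keeps every randomised patient in the comparison. A full analysis set that requires eligibility as well as randomisation allows a patient to leave the primary analysis after allocation. The article does not confine that judgement to facts known before randomisation, and does not say that it is made blind. If an eligibility question were raised because a patient had deteriorated, exclusion would be linked to the outcome. With so few events expected, one or two such decisions matter.

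2. The consent section presumes that eligibility is settled before consent is sought. Several criteria cannot be settled without blood or urine results, and Table 3 presents those tests as trial screening procedures at the same visit as consent. Recruitment {15} describes 46 sites working through fever clinics and emergency departments. An order left unstated can be resolved differently from site to site, and at stake is whether trial-specific tests are done before consent.

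**Working it through.** **Analysis set, by reading**

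- Full analysis set: eligible and randomised.
- Per-protocol set: eligible and further conditions.
- Safety set: enrolled, at least one dose and at least one safety evaluation; used for safety only.

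A patient who is randomised, dosed and later judged ineligible can be in the safety set but fails the definition of both efficacy sets. No defined set consists of everyone randomised.

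**Analysis set, size**

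Inputs are 2.6% and 0.19% from Sample size {14}, and 548 per arm with 10% dropout from Recruitment {15}. The plan's own figure is checked first. With one-sided α = 0.025, 90% power and unpooled variance:

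n per arm = (1.960 + 1.282)² × (0.026 × 0.974 + 0.0019 × 0.9981) / (0.026 − 0.0019)² = 10.51 × 0.02722 / 0.000581 ≈ 493

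Two arms give 986, and 986 / 0.9 ≈ 1096. The stated 986 therefore reproduces as a total. Its description as a per-group number is a separate matter; 548 randomised and 493 evaluable per arm are used here.

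Expected events with 548 per arm:

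- placebo: 548 × 0.026 = 14.2
- azvudine: 548 × 0.0019 = 1.0
- one placebo event removed: 1 / 14.2 = 7.0% of that arm's events

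With 493 per arm the placebo figure is 12.8 events, and one event is 1 / 12.8 = 7.8%.

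Power if a share of randomised patients were removed as ineligible, using Φ{[Δ√n − 1.96√(2p̄(1 − p̄))] / √(p₁q₁ + p₂q₂)} with Δ = 0.0241 and p̄ = 0.01395. The shares are assumptions; the article gives none.

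| Removed (assumed) | n per arm | Expected events, both arms | Power |
|---|---|---|---|
| 0% | 493 | 13.8 | 89.8% |
| 2% | 483 | 13.5 | 89.3% |
| 5% | 468 | 13.1 | 88.3% |
| 10% | 444 | 12.4 | 86.6% |

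The 0% row is 89.8% rather than 90% because this formula pools the variance under the null hypothesis. Power is not the main issue; the weight carried by each event is.

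**Order of steps, side by side**

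| Source | Order implied |
|---|---|
| {26a} | eligibility established, then consent |
| {16a} | eligible patient signs, then randomisation and treatment at once |
| Table 3 | consent, eligibility check and the tests it needs, all in screening; day 1 later |

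The first two agree with each other. The tension is with the third. If the screening tests follow consent, the person signing is not yet known to meet all criteria, and results must come back between signature and randomisation. If they precede consent, procedures listed for the trial are done before agreement to take part. The pregnancy criterion sharpens this: a woman of child-bearing age must give a contraceptive undertaking and have a negative test to meet the inclusion criteria, so {26a} read literally places both before informed consent.

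**The case against.** **On the analysis set.** Since only eligible patients are to be randomised, the word eligible may be mere description that excludes nobody. No section describes removing a patient after randomisation or re-opening an eligibility file. Investigators and patients are blinded, and planned unblinding follows database lock unless the interim analysis shows efficacy. Narrow exclusions judged blind on pre-randomisation data need not bias the comparison. All of this is fair, and actual removal is an inference from the definition. But the article does not state those safeguards. Blinding alone is also not enough if the ruling is prompted by the outcome, because the outcome may itself depend on treatment. The definition and the principle stand in the same section and do not match, so this is not simply detail left to the analysis plan.

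**On the order of steps.** Plans for assessment and collection of outcomes {18a} draws enrolment data from hospital records, so routine-care results might establish eligibility without trial-specific testing before consent. The full protocol may also give the order. This lowers the weight of the point. Still, {18a} describes the source of collected data and does not say that eligibility rests on existing results.

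**Stronger readings that a reader might infer, and why they fail:**

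- *Patients are randomised before eligibility is known.* {16a} randomises eligible patients, and Table 3 puts the eligibility check before day 1. This reading ignores both.
- *A large number of randomised patients, say 55 to 219, would be removed.* That range is an assumed 5–20% laboratory failure rate applied to 1096. Such a rate has no source in the article and would describe screen failures, not randomised patients.
- *A day-5 patient who uses the 24 hours starts on day 6.* {26a} places the decision time before enrolment, and it is an allowance, not a compulsory wait. Nothing says that the symptom limit is fixed at screening.
- *The order of steps causes exclusions from the full analysis set.* No such link is shown. The two points stand apart.

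**Conclusion.** Both points hold, with different weight.

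The analysis-set definition is the more important. As written, a randomised patient later judged ineligible lies outside both the full analysis and per-protocol sets, contrary to the stated intention-to-treat principle. Under the plan's own rates, one placebo event lost this way is about 7% of that arm's events (14.2 expected among 548). How many patients would be affected is unknown. Even an assumed 10% removal would lower power only from 89.8% to 86.6%, so the case rests on possible bias, not on power.

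The order of consent and testing is a smaller inconsistency that needs reconciling. It lies between the consent and randomisation sections on one side and Table 3 on the other. It rests on a literal reading of a condensed article.

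**What to change.** 1. In {20a}, define the full analysis set as all randomised patients, analysed in the arm to which they were randomised. Handle ineligibility found later only in the per-protocol set or a sensitivity analysis, judged blind to allocation and on data from before randomisation. This is a change of wording with no effect on sample size. It should be made before the interim analysis and any unblinding.

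2. In {26a}, {13} with Table 3, and {16a}, state one order: consent before any trial-specific test, then screening tests, then eligibility confirmed, then randomisation. In {26a}, seek consent from potentially eligible patients. In {16a}, tie randomisation to confirmed eligibility rather than to the moment of signing. If routine-care results may be used for eligibility, say so. The cost is a wording change and some hours between consent and randomisation while results return.

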### Concealment mechanism {16b}

In the concealment of the randomization sequence, the block size will be ensured by the web-based randomization system.

### Implementation {16c}

The staff of the central random system will generate the randomization sequence. The intervention will be decided by the randomization system, and the researcher will be blind to the treatment allocation plan.

## Assignment of interventions: blinding

### Who will be blinded {17a}

This was a double-blinded study, which means that researchers and patients will be blinded to the study intervention allocation.

The blinding will be ensured by producing and packaging (the study drug and the placebo cannot be differentiated by their appearances and packages).

A qualified staff member will dispense the study intervention using the IRT system via unique container numbers in the bottles and blister cards provided. Another staff member will verify the dispensing the blinded medication. The participant should be instructed to maintain the product in the bottle and blister cards, as appropriate, provided throughout the course of dosing and return the bottle and blister cards to the site at the next study visit. The study intervention will be administered in a blinded fashion to the participants.

### Procedure for unblinding if needed {17b}

The Interactive Response Technology (IRT) system will be programmed with instructions to maintain blinding. For anticipated and unanticipated serious adverse events, emergency unblinding may be performed only if the investigator must know the treatment grouping information to proceed in the event of an emergency in the subject (e.g. requiring resuscitation). The safety of the participant will always be the primary consideration in making this decision. The reason for unblinding and the date it occurs must be documented in the source documentation and case report form (CRF). The study-specific IRT reference manual and investigational product manual will provide contact information and further details on how to use the IRT system.

Unless efficacy is demonstrated at an interim analysis, the study will be unblinded after the statisticians finalize the statistical plan and the audit report in the data plan and lock the database. Details of the unblinded sponsor staff supporting the independent data monitoring committee (IDMC) and the timing of unblinding will be outlined in the unblinding plan.

## Data collection and management

### Plans for assessment and collection of outcomes {18a}

During the enrolment process, we plan to collect demographic information, including age, height, weight, blood pressure, heart rate, past medical history, smoking history, and laboratory parameters such as leukocytes, neutrophils, creatinine, uric acid, myocardial enzymes, pro-brain natriuretic peptide, hypersensitive C-reactive protein, D-dimer, and viral load upon admission (Table 3). These data are derived from the electronic medical record system of each participating hospital and will be documented on an electronic case report form (eCRF, https://study.cims-medtech.com/CIMS_V5/PlatFrame.aspx). Any AEs, including clinical symptoms and changes in vital signs, such as headache, dizziness, and nausea, and abnormalities observed in laboratory examination, including elevated serum creatinine AST or ALT, will also be documented. The correlation of AEs and the study drug or placebo will be carefully investigated. Furthermore, any changes in the patients’ conditions will be recorded during the follow-up period, which includes the 28th day after admission and up to 6 months.

Patients who are admitted to the hospital will be monitored on a daily basis until either a primary endpoint event occurs or they are discharged. A telephone follow-up will be conducted on the 28th day after admission to gather information about the patients’ survival status. For patients who remain hospitalized beyond 28 days, endpoint events will be recorded on the 30th day of their hospital stay.

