### Outcomes {12}

The primary outcome of this trial is the ratio of COVID-19-related critical illness and all-cause mortality among the two groups within 28 days. COVID-19-related critical illness is defined as a patient who requires mechanical ventilation or extracorporeal membrane oxygenation or a patient maintaining oxygen saturation (SpO_2_) above 90% who requires high-flow oxygen inhalation with a fraction of inspired oxygen (FiO_2_) not less than 60% or requires noninvasive ventilation with a FiO_2_ not less than 60%.

The secondary outcomes are as follows: (1) COVID-19 viral load measured from pharyngeal swabs at the D1, D3, D7, and D14 timepoints, (2) incidence of azvudine-related adverse events (AEs) and serious adverse events, (3) duration of COVID-19-related symptoms, (4) all-cause mortality within 6 months, (5) days of hospitalization and intensive care unit stay, and (6) the ratio of COVID-19-related severe illness defined on the China Formula of Diagnosis and Treatment for COVID-19 (trial version 10). In detail are as follows: (1) shortness of breath with respiratory rate ≥ 30 breaths/min, (2) SpO_2_ ≤ 93% when inhaling air at rest, (3) partial pressure of arterial oxygen/FiO_2_ ≤ 300 mmHg, and (4) progressive worsening of clinical symptoms and obvious lesion progression > 50% on chest imaging within 24 to 48 h.

The safety endpoints consist of adverse events that emerge during or after the treatment period and subsequent observation period until 28 days. SAEs and AEs leading to discontinuation of the trial drug or placebo will be coded according to the definition of severe adverse events published by the FDA (https://www.fda.gov/safety/reporting-serious-problems-fda/what-serious-adverse-event).

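### The outcome-collection section times the primary endpoint from admission, with a day-30 rule for long stays. This conflicts with the 28-day endpoint from randomisation, and dated capture of critical illness after discharge is not specified.

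*Protocol article*

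**What the plan says.** **Endpoint.** Outcomes {12} gives the primary outcome as "the ratio of COVID-19-related critical illness and all-cause mortality among the two groups within 28 days". It defines critical illness by mechanical ventilation, ECMO, or high-flow oxygen or noninvasive ventilation above an inspired-oxygen threshold.

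**Schedule.** Participant timeline {13} runs from randomisation: "After randomization, patients will receive the allocated interventions for 7 continuous days and be followed up for 6 months". Table 3 gives every participant a day-28 telephone visit. On the content of the follow-up visits the text says: "We will collect the patients’ survival status at follow-up visits".

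**Collection.** Plans for assessment and collection of outcomes {18a} uses a different clock: "A telephone follow-up will be conducted on the 28th day after admission to gather information about the patients’ survival status". Admitted patients are "monitored on a daily basis until either a primary endpoint event occurs or they are discharged". For long stays the rule is: "For patients who remain hospitalized beyond 28 days, endpoint events will be recorded on the 30th day of their hospital stay". The section also has a general line that changes in a patient's condition are recorded during follow-up; that line too is timed from admission.

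**Analysis.** Statistical methods {20a} specifies Kaplan-Meier incidence at 28 days, a log-rank test and a Cox model. The missing-data section {20c} censors patients without an event at their last follow-up date and mentions no cut at day 28.

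**The concern.** A time-to-event analysis needs one time origin and one cut-off for everybody. Three timings appear here: 28 days on a randomisation schedule, 28 days after admission, and day 30 of a hospital stay.

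Hospital admission is not a safe stand-in for randomisation. Participants have mild-to-moderate disease, are screened in fever clinics and emergency departments (Recruitment {15}), and may be treated as outpatients (Provisions for posttrial care {30}). Days in hospital are a secondary outcome, so the trial itself treats hospital use as something the drug may change. A window tied to admission would then depend on a post-randomisation event.

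The second issue is ascertainment. Death can be established at any later contact. Critical illness can be established only if someone asks about it and records its date. If that is not done after discharge, a patient who was ventilated on readmission and survived could enter the analysis as event-free.

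**Working it through.** **1. The timings side by side.** Let A be the number of days from randomisation to hospital admission, and suppose that admission does mean hospital admission.

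| Rule | Where | Days after randomisation |
|---|---|---|
| Within 28 days | {12}, {13}, {20a} | 28 |
| 28th day after admission | {18a} | A + 28 |
| 30th day of stay (admission = day 1) | {18a} | A + 29 |

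These agree on the 28-day call only if A = 0, and the day-30 rule differs even then. With A = 10 as an illustration, day 30 of the stay is 39 days after randomisation, which is study day 40 if randomisation is day 1. A participant who is never admitted has no A, so {18a} gives that person no day 28. Both examples depend on the hospital-admission reading.

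**2. Which analyses could be affected.** A Kaplan-Meier estimate read at day 28 on a correct clock ignores later events. The log-rank test and Cox model use all recorded event times unless follow-up is cut. {20c} states no cut, and follow-up continues to 6 months.

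**3. What captures non-fatal events after discharge.**
- Daily monitoring covers inpatients and stops at discharge ({18a}).
- The day-28 call is described by survival status ({18a}, {13}).
- Table 3 lists symptoms and a chest image at day 28. Vital signs and adverse events stop at day 14, and oxygen level appears only at screening.
- The general line on changes in condition names no form of respiratory support and no dates.

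No listed item is a dated record of ventilation, ECMO or high-flow oxygen after discharge, or after day 14 in an outpatient.

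**4. The plan's own sample size, reproduced.** Inputs from Sample size {14} and Recruitment {15}: 2.6% versus 0.19%, one-sided α = 0.025, power 90%, 10% dropout.

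n per arm = (1.960 + 1.282)² × [0.026 × 0.974 + 0.0019 × 0.9981] / (0.026 − 0.0019)² = 493 (rounded up)

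That is 986 in total, and 986/0.9 = 1096, or 548 per arm. This matches the planned enrolment if 986 is the total. {14} words it as per group, which is a separate matter.

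**5. Expected events.**
- At 548 per arm: 548 × 0.026 = 14.2 and 548 × 0.0019 = 1.0, about 15.3 in all. One event is 1/15.3 = 6.5% of the total.
- At 493 per arm, after dropout: 12.8 and 0.9.

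**6. Effect of the two extra days alone.** As an upper bound, assume constant hazard and run every patient to day 30:
- control: 1 − (1 − 0.026)^(30/28) = 2.78%, against 2.60%
- treated: 1 − (1 − 0.0019)^(30/28) = 0.20%, against 0.19%

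At 548 per arm that is about 548 × 0.0018 = 1.0 extra control event. The rule reaches only patients still in hospital beyond 28 days, so the real effect is smaller.

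**7. Effect of missed events.** The documents give no missed share. Assume a share m missed equally in both arms, so both rates are multiplied by (1 − m). Power at 493 per arm, by the normal approximation with pooled variance under the null:

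| m | Expected events, control / treated | Power |
|---|---|---|
| 0% | 12.8 / 0.9 | 89.8% |
| 5% | 12.2 / 0.9 | 88.3% |
| 10% | 11.5 / 0.8 | 86.5% |
| 20% | 10.3 / 0.7 | 82.3% |
| 30% | 9.0 / 0.7 | 76.9% |

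**The case against.** The best defence is that *admission* loosely means entry to the study. The same section speaks of viral load upon admission and points to Table 3, where viral load is due on day 1 for every participant. On that reading the call is simply Table 3's day-28 visit, and the window no longer depends on hospitalisation. This is plausible, but it does not explain the sentence about day 30 of the hospital stay, and a site following the text literally could go either way.

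The day-30 sentence also says when events are recorded, not that events after day 28 count, and the endpoint is fixed at 28 days elsewhere. That is fair. With step 6, it makes the two extra days a minor matter. The analysis plan may also state the day-28 cut.

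On capture, a reader might infer that the call asks about survival and nothing else, or that critical illness is systematically under-recorded. The documents do not say so. Symptoms and a chest image are listed at day 28, changes in condition are to be recorded, safety endpoints run to day 28, and days in hospital and intensive care must be collected for a secondary outcome. An article may also leave form items out. What stands is narrower: the text gives the call a stated purpose that covers one component of the composite, and nothing listed specifies the other component with dates.

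A reader might also count the 3-day tolerance around the day-28 call as a defect. It is ordinary visit tolerance: censoring at last contact deals with an early call, and survival status is collected again at 3 and 6 months.

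**Conclusion.** The point holds as a contradiction in the text and a gap in specified endpoint capture. Followed literally, {18a} gives unequal event windows, daily endpoint monitoring that ends at discharge and a day-28 call aimed at survival status, against an endpoint of 28 days on a randomisation schedule.

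The clock origin and the capture of non-fatal events carry the weight; the two extra days do not. The study-day-40 example and the participant without a day 28 should not be taken as established, since both fail if admission means study entry. Nor do the documents show that any event has been or will be lost. The power figures (86.5% at 10% missed, 76.9% at 30%) rest on an assumed, equal missed share and on the plan's own event rates. With about 15 events expected, a few missed or misplaced ones would matter.

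**What to change.** - State randomisation as the single time origin. Count primary events up to study day 28 for every participant, and censor there in the log-rank and Cox analyses as well as the Kaplan-Meier estimate.
- In {18a}, replace the references to time after admission, and the day-30 sentence, with that rule.
- At the scheduled day-28 call, ask every randomised participant, including those discharged or never admitted, for vital status and for any admission, high-flow oxygen, ventilation or ECMO since last contact, with dates.

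The cost is protocol wording and one eCRF page at a call already planned. The sample size does not change, because 2.6% and 0.19% are taken as day-28 rates: 493 per arm, 986 in total and 1096 after dropout all stand. The change is best made while participants are still in follow-up, because dates of respiratory support may be hard to recover later.
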